### Main analysis

Statistical analysis will be conducted based on the intention-to-treat principle. A two-level (staff nested within residential settings) analysis of covariance (ANCOVA) will be fitted to provide a between-group comparison of mean SECBQ scores at 20-weeks post-randomisation follow-up, adjusted for baseline SECBQ scores. The analysis will also adjust for residential setting size and region (stratification factors at randomisation).

Secondary outcomes measured at the staff level (self-efficacy, similarity and empowerment attitudes, work stress and positive experiences) will be analysed as above; two-level ANCOVA will be fitted to measures at follow-up, adjusted for the corresponding baseline covariates, region and residential setting size. Secondary outcomes measured at the residential setting level (incidents of aggressive CB and incidents of recorded restraint procedures) will be analysed using an appropriate single level regression analysis that adjusts for baseline levels of the outcome, region and residential setting size.

All main statistical analysis will be conducted on complete cases (i.e. all randomised residential settings and staff providing follow-up data). However, to investigate the impact of missing outcome data on the conclusions drawn from the trial, missing mechanisms will be explored and appropriate imputation methods applied via sensitivity analyses. Baseline characteristics will be presented by trial arm. The WCW training fidelity data will be summarised descriptively for inclusion in the main results paper.

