### Intervention – WCW training programme

Following baseline, those allocated to receive the intervention will attend a training session (anticipated up to 12 staff per session). Those allocated to the waiting list control will be informed that their training session will available to them after the 20 week follow-up data collection time point (Fig. 2).

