**Fig. 2 Fig2:**
[figure not shown]
Summary flow chart (Note: Process repeated to recruit a total of 118 residential settings)

The training is a half-day session delivered by a trainer with ID and CB supported by a trainer without ID. WCW was developed jointly with people with ID and CB and the training course is fully manualised. Trainers with ID and CB are trained to deliver WCW using a process that is also manualised (Co-Trainer Training). WCW training covers the following topics (from the perspective of people with ID and CB):Communication and how staff listening can prevent escalation of CBHow the living environment contributes to frustration and CBThe experience of being physically restrainedWhat it is like to be on medication ‘for’ CBExperiences of feeling excluded because of CBUnhelpful attitudes and behaviour of support staff, and a discussion of positive qualities that contribute to good support/care

At the end of the WCW training session, attendees write an Action Plan of what they will do differently in their service on return. These plans are shared with the group for feedback from the trainers and other attendees. Following WCW training, the trainer without ID will contact each residential setting manager/lead for a 30 min coaching session (telephone, Skype or similar voice connection system). The trainer will follow a standard protocol for this coaching session to finalise the Action Plan and how this will be introduced to, adjusted and then agreed with the staff team (e.g. as a part of a regular team meeting). After the Action Plan has been agreed with the team, a further 30 min coaching session will focus on the implementation and monitoring of the Action Plan. WCW training ends with this second coaching session.

In summary, WCW training includes four core components, namely (1) staff from a residential setting attend a half day training course; (2) these staff develop an initial Action Plan for their setting that is shared with the group receiving the training and the trainers; (3) the trained staff then receive an individualised short coaching session focused on how to disseminate the messages from the training and agree an Action Plan with the whole staff team of the residential setting; and (4) a follow-up coaching session on how to implement the agreed plan and to monitor its implementation (including the need for ongoing review with the staff team). Thus, WCW is not just a half-day training course.

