### Adherence

Following the 20-week post-randomisation data collection, the research assistant (RA) will code the first eight WCW training sessions (audio-recorded) for fidelity of delivery according to the manual. This will be done using a checklist developed from the manual. Each WCW training element will be rated 0–2 (0 = missing, 1 = partially delivered, 2 = fully delivered according to the manual). All eight training sessions will be coded for inter-rater agreement by the chief investigator. Once inter-rater reliability has been established, the RA will go on to code fidelity for the remaining eight training sessions.

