### Sample size determination

The sample size calculation is based on the results from Hutchinson et al. [12], where an effect size of 0.50 (standardised mean difference) for the staff empathy score (primary outcome) was observed. With alpha set at 0.05 and power at 90%, the unadjusted sample size required is 172 (86 per arm) staff. With cluster size as two staff per residential settings and allowing an intracluster correlation of 0.10, the variance inflation factor is 1.1. Therefore, a total of 189 staff are needed (95 per trial arm). Building in a 20% loss to follow-up means an estimated 237 staff are required. This calculation is the basis for the sample size for this study of 118 residential settings.

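### WCW is taught in sessions shared by several settings, in one arm only, but the primary model clusters by setting alone; if outcomes correlate within sessions, its standard error is too small

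*Protocol article*

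**What the plan says.** The Main analysis section of the protocol article names the levels of the primary model: "A two-level (staff nested within residential settings) analysis of covariance (ANCOVA) will be fitted to provide a between-group comparison of mean SECBQ scores". Staff-level secondary outcomes are analysed the same way. No term for training session or trainer appears.

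The Intervention section says that staff in the WCW arm "will attend a training session (anticipated up to 12 staff per session"). Two staff come from each setting and attend together (Table 1), so a full session holds six settings. The groups interact. Attendees write Action Plans, and "These plans are shared with the group for feedback from the trainers and other attendees". Waiting-list settings are offered training only after the 20-week follow-up, which is the primary time point.

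The Adherence section gives the likely number of sessions. Eight are coded first, and then "the RA will go on to code fidelity for the remaining eight training sessions", which makes 16.

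The Sample size section allows for one source of clustering: "With cluster size as two staff per residential settings and allowing an intracluster correlation of 0.10, the variance inflation factor is 1.1".

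**The concern.** Staff from different settings who sit in the same session share the trainers, the discussion and the comments on their plans. A good or poor session can therefore move several settings together. This happens in the WCW arm only, so the comparison is partially nested: staff within settings in the control arm, and staff within settings within sessions in the WCW arm.

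A random intercept for setting captures what the two colleagues share, but it treats settings from the same session as independent. With any positive session correlation, the WCW mean is less precise than the model reports. The confidence interval for the primary outcome is then too narrow, and the test rejects a true null hypothesis more often than 5% of the time. The power calculation has the same gap.

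**Working it through.** **The plan's own figures.** The inputs are in the Sample size section: "an effect size of 0.50 (standardised mean difference) for the staff empathy score (primary outcome) was observed", and "With alpha set at 0.05 and power at 90%, the unadjusted sample size required is 172 (86 per arm) staff". A two-sided t-based calculation gives 85.03 per arm, rounded up to 86, or 172 in total. Then 172 × 1.1 = 189.2, matching "a total of 189 staff are needed (95 per trial arm"), and 189 / 0.8 = 236.25, rounded up to 237. The stated figures reproduce. With 118 settings (236 staff) and 20% loss, n = 236 × 0.8 / 2 = 94.4 staff are analysed per arm. The standard error is √(2 × 1.1 / 94.4) = 0.1527, and power is Φ(0.5/0.1527 − 1.96) = 90.6% with setting clustering only.

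**Session size.** The WCW arm has 59 settings, or 118 staff.
- 16 sessions (assuming that all 16 coded sessions are WCW-arm sessions): 118 × 0.8 / 16 = 5.9 analysed staff per session.
- 10 sessions (118 / 12 = 9.8, rounded up): 118 × 0.8 / 10 = 9.44.

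**Variance with a session effect.** Let ρ be the session ICC, added to the setting ICC of 0.10, and m the analysed staff per session.
- WCW design effect: 1.1 + (m − 1)ρ. Control design effect: 1.1.
- True SE = √([2.2 + (m − 1)ρ] / 94.4).
- Type I error of the setting-only analysis = 2[1 − Φ(1.96 × model SE / true SE)].

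The model SE can be taken in two ways. (a) Setting ICC held at the planned 0.10: √(2.2 / 94.4). (b) As the fitted model would estimate it. Two colleagues also share their session, so the estimated setting variance in the WCW arm rises by ρ, giving √((2.2 + ρ) / 94.4).

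Worked example, 10 sessions and ρ = 0.05: the WCW design effect is 1.1 + 8.44 × 0.05 = 1.522 and the true SE is √(2.622 / 94.4) = 0.1667. Under (a), the ratio is 0.1527 / 0.1667 = 0.916 and type I error is 7.3%. Under (b), the model SE is √(2.25 / 94.4) = 0.1544 and type I error is 6.9%. Power with the correct SE is Φ(0.5/0.1667 − 1.96) = 85.1%.

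| Sessions | Session ICC (assumed) | True SE | Type I error (a) | Type I error (b) | Power, correct SE |
|---|---|---|---|---|---|
| 16 | 0.01 | 0.1544 | 5.3% | 5.2% | 90.0% |
| 16 | 0.02 | 0.1560 | 5.5% | 5.4% | 89.3% |
| 16 | 0.05 | 0.1609 | 6.3% | 6.0% | 87.4% |
| 16 | 0.10 | 0.1688 | 7.6% | 7.0% | 84.2% |
| 10 | 0.01 | 0.1556 | 5.4% | 5.4% | 89.5% |
| 10 | 0.02 | 0.1584 | 5.9% | 5.8% | 88.4% |
| 10 | 0.05 | 0.1667 | 7.3% | 6.9% | 85.1% |
| 10 | 0.10 | 0.1796 | 9.6% | 8.8% | 79.5% |

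Simulated t-tests on setting means, with 47 settings per arm (40,000 runs), agree with (b): 5.1 / 5.4 / 6.0 / 7.1% with 16 sessions and 5.3 / 5.6 / 6.9 / 8.8% with 10.

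**Baseline adjustment.** The sample size takes no credit for the planned baseline covariate. Assume a baseline correlation of 0.5 (not in the documents), so that all variance except the session part is multiplied by 1 − 0.25 = 0.75. For 10 sessions and ρ = 0.05, the WCW term is 9.44 × 0.05 + 0.75 × (1.1 − 0.05) = 1.2595 and the control term is 0.825. The true SE is √(2.0845 / 94.4) = 0.1486, and power is 92.0%. The fitted-model sum is 0.825 + 2 × 0.05 + 0.7875 = 1.7125. The SE ratio is √(1.7125 / 2.0845) = 0.906, and type I error is 7.6%, against 6.9% without the covariate. Power recovers, but the SE problem does not, because session effects arise after baseline.

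**The case against.** The strongest reply is that nothing in the documents shows a session effect of any size. Delivery is fully manualised, and each setting then has two coaching contacts of its own and agrees its Action Plan with its own team. All of this may keep session variance small, and at an ICC of 0.01 the effect is trivial. That stands: the point is conditional and its size is assumed.

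A reader might infer that the stated 90% power is wrong. The documents do not support that. The arithmetic is correct for setting clustering, and the uncredited baseline adjustment could restore the loss.

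A reader might also add the inflated type I error to the lower power as two penalties. They belong to different analyses. At a standardised difference of 0.50, with 10 sessions and a session ICC of 0.10, the planned test still rejects with probability Φ((0.5 − 1.96 × 0.1561) / 0.1796) = 86.0%; the 79.5% applies to the corrected model.

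Extending the claim to setting-level incident and restraint outcomes is tempting too. The article leaves that regression open and no calculation was made for it, so it is not claimed here.

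Finally, an analysis plan that is not shown may contain a session sensitivity analysis. The article does not rule one out. It does, however, fix the levels of the primary model, and those levels omit a grouping that its own delivery section creates.

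**Conclusion.** The point holds in conditional form. Sessions span settings in the WCW arm only, and the fixed primary model does not represent them. For any positive session ICC, its standard error is too small and type I error exceeds 5%. Over assumed ICCs of 0.01 to 0.10, the error rate is about 5.3 to 7.6% with 16 sessions and 5.4 to 9.6% with 10 when the setting ICC is held at 0.10. It is 5.2 to 7.0% and 5.4 to 8.8% when the fitted model absorbs what it can.

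These figures rest on the assumed ICCs, equal session sizes, 20% loss spread evenly, normal approximations and no baseline credit. Trainer-level clustering could add to them but cannot be computed, because the number of trainers is not stated. A power shortfall is possible but not established. This is a worthwhile and inexpensive improvement, not a fatal flaw.

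**What to change.** Record which session each WCW setting attended. Fit the primary outcome with a partially nested model: a setting random intercept in both arms, a session random effect in the WCW arm only, and Kenward-Roger or Satterthwaite degrees of freedom. Report the estimated session ICC. Use the same model for staff-level secondary outcomes, which follow the primary analysis.

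In the Sample size section, keep 90% as the power with setting clustering only. Add that, before any gain from baseline adjustment, power under the partially nested model is about 84–90% with 16 sessions or 80–90% with 10, for session ICCs of 0.01 to 0.10. State that baseline adjustment may recover this loss but does not correct the standard error.

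The cost is one identifier, which attendance should already give, one random term and a few sentences. The downsides are a slightly wider confidence interval and a session variance estimated imprecisely from 10 to 16 sessions. No extra recruitment is needed.

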### Study design

The trial will be a cluster randomised controlled trial. Overall, 118 residential settings will be recruited into the trial and randomised to the either the WCW training arm or to a waiting list control group. At each residential setting, two members of staff will be recruited; one manager/lead staff member along with one other support staff member. In both arms of the trial, those staff taking part will continue to receive training as usual (on ID social care and specifically on CB if provided) following their organisations’ ongoing staff development policies. Recruitment will be in two phases with approximately 58–60 residential settings per phase. Phase 2 of the trial will immediately follow the 20 week data collection time point for phase 1. Randomisation will occur at one point in time for each phase and will be carried out by a study-independent statistician from the Centre for Trials Research using a dynamic balancing algorithm specifically designed for cluster randomised trials [17]. Allocations will be stratified by residential setting size, geographical region and phase of recruitment (i.e. phase 1 or 2) in a ratio of 1:1. A Standard Protocol Items: Recommendations for Interventional Trials (SPIRIT) checklist is provided in Additional file 1.

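### Recruitment phase is a stratification factor at randomisation but is missing from all three main model specifications; the cost is conservative, probably small, and free to remove

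*Protocol article*

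**What the plan says.** All of the text is in the protocol article.

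- **Study design, allocation:** "Allocations will be stratified by residential setting size, geographical region and phase of recruitment (i.e. phase 1 or 2) in a ratio of 1:1".
- **Study design, timing:** "Randomisation will occur at one point in time for each phase". "Recruitment will be in two phases with approximately 58–60 residential settings per phase", and "Phase 2 of the trial will immediately follow the 20 week data collection time point for phase 1".
- **Main analysis, primary outcome:** a two-level ANCOVA of the empathy score (SECBQ) at 20 weeks, adjusted for baseline SECBQ, with this addition: "The analysis will also adjust for residential setting size and region (stratification factors at randomisation").
- **Main analysis, staff-level secondary outcomes:** the same type of model, "adjusted for the corresponding baseline covariates, region and residential setting size".
- **Main analysis, setting-level secondary outcomes** (aggressive incidents and restraint): a "single level regression analysis that adjusts for baseline levels of the outcome, region and residential setting size".

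Phase appears in none of the three specifications, and no reason is given for leaving it out.

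**The concern.** The wording in Main analysis shows an intention to adjust for the factors used at randomisation, but one of the three has dropped out. Phase is built into this design: each phase has its own randomisation, and the second starts only after the 20-week data of the first.

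Forcing balance on a factor removes its contribution to the true sampling variability of the treatment contrast. If the model then omits the factor, whatever variation it explains stays in the residual. The reported standard error is then larger than the true one, the confidence interval is wider than it need be, and the test rejects less often than its nominal level. At stake is some precision and power on the primary and secondary outcomes. The covariate set should also be settled before results are seen, because adding phase afterwards could look like a post hoc choice.

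**Working it through.** **1. The plan's own sample size.** Inputs from Sample size determination: effect 0.50 SD, alpha 0.05 (taken as two-sided), power 90%, two staff per setting, intracluster correlation 0.10, 20% loss.

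- Unadjusted: the t-based calculation gives 86 per arm, 172 in total.
- Design effect: 1 + (2 − 1) × 0.10 = 1.1, and 172 × 1.1 = 189.2, so 189.
- After loss: 189 / 0.8 = 236.25, so 237 staff; 237 / 2 = 118.5, in line with 118 settings.

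The stated figures reproduce, and this point does not change them.

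**2. Covariates side by side.**

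| Factor | Randomisation | Primary model | Staff-level secondary | Setting-level secondary |
|---|---|---|---|---|
| Setting size | yes | yes | yes | yes |
| Region | yes | yes | yes | yes |
| Phase | yes | no | no | no |

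**3. Effect on the standard error.** Let g be the difference between phases in SD units, conditional on the other covariates. The article gives no value, so g is an assumption. With two phases of nearly equal size, omitting phase adds g²/4 to the variance of a setting mean, v. The ratio of the model standard error without phase to that with phase is

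R = √[(v + g²/4) / v].

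With arms balanced within phase, the true standard error does not change. Hence type I error = 2 × [1 − Φ(1.96 R)] and power = Φ(λ − 1.96 R), where λ is the effect divided by its true standard error.

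**4. No baseline adjustment, as in the sample size section.** v = (1 + 0.10)/2 = 0.55. With 189 analysed staff (94.5 per arm) the standard error is √(2 × 1.1 / 94.5) = 0.1526, so λ = 0.50 / 0.1526 = 3.277. Power with phase included is Φ(3.277 − 1.96) = 90.6%.

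| g (SD, assumed) | g²/4 | R | Type I error | Power, phase omitted |
|---|---|---|---|---|
| 0 | 0 | 1.000 | 5.0% | 90.6% |
| 0.2 | 0.0100 | 1.009 | 4.8% | 90.3% |
| 0.3 | 0.0225 | 1.020 | 4.6% | 89.9% |
| 0.5 | 0.0625 | 1.055 | 3.9% | 88.7% |

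**5. With an assumed baseline correlation of 0.5.** Residual variance falls to 1 − 0.5² = 0.75, so v = 0.75 × 0.55 = 0.4125. Starting from the nominal 90% (1.2816 + 1.96 = 3.2416), λ = 3.2416 / √0.75 = 3.743. Power with phase included is Φ(3.743 − 1.96) = 96.3%.

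| g (SD, assumed) | R | Power, phase omitted |
|---|---|---|
| 0.2 | 1.012 | 96.1% |
| 0.3 | 1.027 | 95.8% |
| 0.5 | 1.073 | 94.9% |

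**6. Check by simulation.** 118 settings (58 + 60), arms balanced within phase, ANCOVA on setting means, baseline correlation 0.5, 10,000 runs per scenario. The standard error ratio was 1.000, 1.012 and 1.075 at g = 0, 0.2 and 0.5. Type I error with phase omitted was 5.3%, 4.6% and 3.7%. With the true effect set to 0.35 SD, so that a loss of power would be visible, power with phase omitted was 83.4%, 82.7% and 79.7%, against 83.4% with phase included.

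**The case against.** The strongest case for leaving the plan alone has four parts.

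- **The harm is conditional and conservative.** If phase does not predict outcome once baseline, size and region are in the model, nothing is lost. Otherwise the linear estimate is still unbiased and type I error stays at or below nominal. This stands, and it limits the severity.
- **Much of any phase difference is already absorbed.** Baseline is measured within the same phase, so a stable difference in level is partly removed, and region is in every model. A residual difference of 0.5 SD would equal the whole assumed treatment effect. This also stands, and it makes the lower rows of the tables the more credible ones.
- **The parenthesis is not literally false.** Size and region are stratification factors, and the text does not say they are the only ones. That is fair as a reading of the words, but the covariate lists themselves omit phase three times.
- **An analysis plan not shown could add phase.** It could. But the article is not silent: it fixes a covariate set, and a plan with phase would then differ from it.

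A reader might infer more than the text supports. That the standard errors are certainly too wide does not follow, because no phase effect is given. That growing trainer experience is a reason for the adjustment does not follow either: before 20 weeks only the intervention arm is trained, so such a difference would be mainly a treatment-by-phase interaction, which a phase main effect does not model. That the incident outcomes are especially exposed cannot be shown, because their regression type is not specified and the linear result need not carry over exactly. The mediation and subgroup analyses list no covariates, so the point does not extend to them.

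**Conclusion.** The mismatch is established from the text: three factors govern allocation and two enter the main models. Its consequence is a possible loss of precision and power, with no risk of inflated false positives in the linear models.

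For assumed phase differences up to 0.3 SD, the standard error is inflated by no more than about 2% to 3% and power falls by less than one percentage point. At 0.5 SD the inflation is 5.5% without baseline adjustment and 7.3% with an assumed baseline correlation of 0.5; the power loss is just under 2 points (90.6% to 88.7%) or about 1.4 points (96.3% to 94.9%).

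These figures rest on the article's effect size and intracluster correlation, two analysed staff per setting, near-equal phases, balance of arms within phase, and assumed values for the phase effect and baseline correlation. Severity is low to moderate. It is worth correcting because the correction is free, not because the trial's conclusions are at risk.

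**What to change.** Before analysis, add recruitment phase (1 versus 2) as a fixed effect to the primary ANCOVA, to each staff-level secondary ANCOVA, and to both setting-level regressions (aggressive incidents and restraint). Reword the sentence in Main analysis so that setting size, region and phase of recruitment are all named as the stratification factors. If phase is left out on purpose, state the reason.

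The cost is one covariate, about one degree of freedom among 118 settings, and one sentence. No new data are needed and the sample size does not change.

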### Eligibility criteria

Residential settings and staff must fulfil all of the inclusion criteria and none of the exclusion criteria as detailed in Table 1. For homes found to be ineligible at screening, basic demographic data regarding reasons for non-eligibility will be recorded on screening logs.

**Table 1 Tab1:** Inclusion and exclusion criteria

Inclusion criteria for residential settings:	Exclusion criteria for residential settings:
Provides services via English/Welsh publically funded contracts (Local Authorities, Clinical Commissioning Groups)	‘Inpatient’ hospital facility (typically NHS or independent providers)
Provides support to between one and 10 people with intellectual disability (ID)	The manager does not receive approval from the service provider organisation for the residential settings to be a part of the study
Provide at least some 24-h support for people with ID	
Is in a community location	
Provides care for at least one person with ID who engages in aggressive challenging behaviour	
Manager (or equivalent lead staff member) and one other support staff member can be released to attend a ‘Who’s Challenging Who?’ training session together	
Inclusion criteria for staff:	Exclusion criteria for staff:
One staff member will be the manager or other lead staff member (as defined by the service provider organisation)	Staff do not provide their consent to take part in the research
The second staff member will be a direct support worker whose role is no more than 50% in administrative/staff management tasks	Inadequate English reading skills prevent completion of the questionnaire measures
Both staff work at least a 0.70 full time equivalent or more	

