#### Secondary outcome measures

Challenging Behaviour Self-Efficacy Scale [20] (5 items: 1 minute); Similarity and Empowerment attitude scales from the Community Living Attitude Scales [21] (25 items: 5 minutes); Maslach Burnout Inventory – Human Services version [22] (22 items: 5 minutes); Short version [23] of the Staff Positive Perceptions Questionnaire [24] (11 items, 2–3 minutes); and recorded incidents of challenging behaviour and use of restrictive practices in each residential setting.

Measures for staff self-report will be administered in the form of a questionnaire. Additional measures focused on CB incidents and use of restrictive practices at the residential setting level will be included for residential setting managers to complete. To capture these data, we will use definitions developed to capture the same outcomes in earlier research on aggressive behaviour in ID settings [25, 26]. Although incident data are recorded using varied systems, our methodology captures data according to decision rules that can be used with any system typically in use. A similar data extraction and coding system will be used to count use of restraint procedures recorded in the residential settings across all users. In both methods, incidents over the 16 week period preceding data collection points will be included. In addition to the measures listed, a short staff demographic details questionnaire (e.g. age, sex, qualifications, work role) will be included for staff at baseline.

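### Staff role is fixed by design and recorded at baseline but is not a covariate in the two-level ANCOVA; adding it would be a nearly free safeguard against a small, conditional bias

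*Protocol article*

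**What the plan says.** The Protocol article fixes the make-up of every cluster under Study design: "At each residential setting, two members of staff will be recruited; one manager/lead staff member along with one other support staff member". Table 1 under Eligibility criteria enforces it: "The second staff member will be a direct support worker whose role is no more than 50% in administrative/staff management tasks". Role is also recorded, since under Secondary outcome measures "a short staff demographic details questionnaire (e.g. age, sex, qualifications, work role) will be included for staff at baseline".

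Main analysis then states the primary model: "A two-level (staff nested within residential settings) analysis of covariance (ANCOVA) will be fitted to provide a between-group comparison of mean SECBQ scores" at 20 weeks, "adjusted for baseline SECBQ scores". The remaining covariates follow: "The analysis will also adjust for residential setting size and region (stratification factors at randomisation". The staff-level secondary outcomes get the same model with their own baseline scores. Staff role is in neither covariate list, nor among the example subgroup factors under Exploratory analysis. The main analysis uses complete cases, with imputation as a sensitivity analysis, and the sample size allows for 20% loss.

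**The concern.** The two people in a home are not interchangeable, because one is always the manager or lead and the other always a support worker. A difference in mean empathy between the roles that the baseline score does not absorb is counted by the model as random variation within homes. This has two possible consequences.

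- The estimated ICC falls. That matters mainly to anyone who uses this trial's ICC to plan another.
- Role cancels from the arm comparison only where both members of the pair are analysed. If losses within a home are independent (an assumption), 20% loss leaves 2 × 0.2 × 0.8 = 32% of homes, about 38 of 118, with one person. If managers are over-represented among those lost in one arm but not in the other, the arm contrast picks up part of the role difference.

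Uneven loss is conceivable. Under the intervention section, the coaching calls go to the manager or lead and take place only in the WCW arm, so WCW managers have study contact that nobody else has. The documents do not say that retention will differ for this reason.

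**Working it through.** **Inputs from the Protocol article.** 118 homes, 1:1 allocation, two staff per home (one of each role), ICC 0.10, effect 0.50 SD, alpha 0.05, power 90%, 20% loss, complete-case analysis.

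**Assumed, because the documents do not give them.** The role difference d left after baseline adjustment (in SDs of the outcome, total variance set to 1), and loss by role and arm.

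**1. The plan's own figure.** A two-sided t-test with d = 0.50 needs 85.03, so 86 per arm and 172 in all. Design effect 1 + (2 − 1) × 0.10 = 1.1; 172 × 1.1 = 189.2; 189/0.8 = 236.25, rounded up to 237; 118 × 2 = 236. The stated chain reproduces. A role term does not alter it, because role is balanced in every home.

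**2. ICC, complete pairs.** The between-home mean square is 1 + ICC, with or without role. The within-home mean square without role is (1 − ICC) + d²/2. Hence apparent ICC = (2·ICC − d²/2)/(2 + d²/2). With ICC = 0.10:
- d = 0.2: (0.20 − 0.02)/2.02 = 0.089
- d = 0.3: (0.20 − 0.045)/2.045 = 0.076
- d = 0.5: (0.20 − 0.125)/2.125 = 0.035

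**3. Bias with loss.** Bias = d × (manager share analysed in WCW − manager share in control). Loss is written manager/support worker.
- Same loss by role in both arms: shares equal, bias 0.
- 10%/30% in WCW, 20%/20% in control: 0.9/1.6 − 0.5 = 0.0625; bias 0.013 (d = 0.2) or 0.031 (d = 0.5).
- 10%/30% against 30%/10%: 0.5625 − 0.4375 = 0.125; bias 0.025 or 0.063.
- Extreme, 0%/40% against 40%/0%: 0.625 − 0.375 = 0.25; bias 0.05 or 0.125.

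**4. Simulation check.** 118 homes, ICC 0.10, no true effect, REML random intercept, 1,500 trials per setting, d = 0.5:

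| Loss, WCW; control | Role term | Mean ICC | Bias | Mean SE | Type I error |
|---|---|---|---|---|---|
| none | no | 0.058 | −0.003 | 0.138 | 0.043 |
| none | yes | 0.107 | −0.003 | 0.137 | 0.047 |
| 20/20; 20/20 | no | 0.065 | 0.004 | 0.154 | 0.040 |
| 20/20; 20/20 | yes | 0.112 | 0.004 | 0.152 | 0.041 |
| 10/30; 10/30 | no | 0.067 | 0.000 | 0.154 | 0.043 |
| 10/30; 10/30 | yes | 0.112 | 0.000 | 0.152 | 0.042 |
| 10/30; 30/10 | no | 0.071 | 0.064 | 0.154 | 0.064 |
| 10/30; 30/10 | yes | 0.117 | −0.002 | 0.153 | 0.048 |

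Monte Carlo error is about 0.154/√1500 = 0.004 for bias and √(0.05 × 0.95/1500) = 0.006 for type I error. The simulated mean ICC without role and without loss (0.058) exceeds the formula's 0.035 because REML estimates cannot go below zero. The SE without role is larger by 0.1380/0.1369 = 1.008 with no loss and 0.1538/0.1518 = 1.013 with 20% loss.

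**5. Allowing for the baseline score explicitly.** Take a baseline correlation of 0.5 and a raw role difference D present at both times. Without role, the baseline slope is b = (0.5 + D²/4)/(1 + D²/4), and D(1 − b) remains: 0.147, 0.235 and 0.345 for D = 0.3, 0.5 and 0.8. Suppose managers lose 20% in WCW and 10% in control, and support workers 15% and 30%. The shares are 0.8/1.65 = 0.485 and 0.9/1.6 = 0.5625, a difference of −0.078. The bias is then −0.011, −0.018 and −0.027. Simulation gave −0.016, −0.023 and −0.025 without role and −0.003, −0.004 and +0.002 with it, so the differences are −0.013, −0.019 and −0.027, in agreement.

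**The case against.** The strongest reply is that nothing here is misstated. The quoted sentence concerns stratification factors, and role is not one. Adjusting for baseline score and stratifiers is a coherent model, and further prognostic covariates are often named in an analysis plan, which is not shown. This stands to the extent that the point cannot be called an error. It does not remove the point, because Main analysis states a specific covariate list and role could be added to it now.

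A reader might infer that an understated ICC makes the treatment SE too small. The documents do not support that. With one of each role per home, role cancels from the home means, the between-home mean square is unchanged, and the SE errs slightly on the large side.

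A reader might also infer that losing one of a pair is enough to bias the comparison. It is not. Loss that is uneven by role but alike in both arms gives no bias. The bias needs both a residual role difference and a role-by-arm pattern of loss, and the documents report neither.

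Two further objections partly stand. Estimating the ICC is not a trial objective, and a role term does not give an exact ICC: at a raw role difference of 0.8 SD with 20% loss, the mean estimate was 0.115 with role and 0.082 without, against a true 0.10. The planned imputation analyses could also use role, although the text does not say that they will.

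**Conclusion.** The point holds as a low-severity improvement. If scores differ by role beyond what baseline explains, the model as listed lowers the estimated ICC and makes the treatment SE about 1% conservative. If the role mix of those lost also differs between arms, the complete-case arm effect is biased by roughly 0.01 to 0.06 SD under the moderate patterns examined. The deliberately extreme pattern with d = 0.5 reaches 0.125 SD. The planned effect is described as "an effect size of 0.50 (standardised mean difference) for the staff empathy score (primary outcome) was observed", so 0.06 SD is about 12% of it (0.0625/0.50), and the type I error in that setting was 0.064 without role and 0.048 with it. Without either condition the arm comparison is sound.

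All sizes rest on an assumed residual role difference, assumed loss patterns and, in step 5, an assumed baseline correlation of 0.5. They were worked for one continuous outcome. The secondary staff-level outcomes share the model but may differ in size.

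**What to change.** Prespecify staff role (manager or lead versus direct support worker) as a fixed effect in the two-level ANCOVA for SECBQ and for every staff-level secondary outcome. Role is already collected and is balanced in every home, so no new data are needed and the sample size stays as it is. The cost is one degree of freedom out of roughly 185 and one phrase in the analysis text. Deciding now also avoids a post hoc covariate choice should attrition prove uneven by role.

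The term has a limit that should be acknowledged. If the training effect itself differs by role, unequal loss by role shifts the average effect, and a main-effect term does not correct that. Reporting follow-up by role and arm would show whether the question arises.
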